## Research design and methods

### Study design

The current study is a multi-centre, prospective, randomised, non-blind, superiority parallel arm trial comparing a stepped-care model of stand-alone DBT group skills therapy with treatment as usual. The subject of this evaluation is a two-step care model that was developed to address the finite resources within local community mental health services (see Fig. 1 for the trial design flow chart). Referrals for treatment will be made through a central mental health intake line or emergency department. All participants will complete a diagnostic assessment to determine suitability for the study. Following recruitment, participants will be randomly allocated to one of the two conditions. The treatment condition (group skills therapy) will be a manualised DBT programme.

**Fig. 1 Fig1:**
[figure not shown]
Proposed trial design evaluating stepped group skills training interventions. Note. *All participants will be contacted 16 weeks post-intervention, independent of the number of sessions completed. **Number of participants expected at each time point (inclusive of a dropout rate of 30%)

The group skills treatment will involve two steps. The treatment group will be offered a weekly, 2-h group treatment for 12 weeks. Following completion of the 12-week group, suitability for inclusion in the second step of group treatment (16-week skills group) will be assessed based on group attendance and clinical indicators: criteria for inclusion in continuing treatment includes meeting > 4 BPD diagnostic criteria or severity on GAF (< 65) at the completion of the 12-week group. Similarly, participants in the TAU condition will be retained in treatment through the additional 16-week period based on clinical need.

DBT targets the development of skills in mindfulness, emotional regulation, distress tolerance and interpersonal effectiveness [17]. Two separate group treatment manuals will be developed for the treatment condition. The manualised treatments will be based on the DBT skills and provide structured therapeutic intervention. The 12-week manual will provide an introduction to target skills and an opportunity to practise within the group. Participants will be encouraged to practise skills between sessions and provide feedback in the following session. The 16-week manual will expand on skills introduced in the 12-week manual. It will be delivered in a similar format, including in-session and between-session practice with a review.

Treatment as usual (TAU) refers to typical care provided by the trial sites. Participants randomised to this condition will be referred to the care pathways typically used by the public mental health site. These referrals will be informed by clinical decision-making and the presenting issues of the participant. As such, a range of treatment settings may be accessed in the TAU condition including case management within the local community mental health service, mental health rehabilitation services, referral to a local private psychologist or psychiatrist with known experience in working with BPD, local non-government organisations, general practitioners (GPs) and family and carer services. The TAU referral pathway will be specifically tailored to the participant presentation.

### Study setting

Treatment will be provided at two local community mental health sites. They are as follows: (1) the Illawarra Community Mental Health Service, which is located in Wollongong, NSW, Australia. Wollongong is a coastal regional city with an estimated population of 216,071 [1]; (2) the Campbelltown Community Mental Health Service is located in Campbelltown, NSW, Australia. Campbelltown is located in the south-western suburbs of Sydney, NSW, and has an estimated population of 170,943 [4]. The median income levels for both sites are reportedly below the Australian median income level. Approximately 80% of participants will be recruited at trial site 1 with the remaining 20% recruited at trial site 2.

This study uses a collaborative multi-method approach between NSW Health clinicians and clinical researchers at the University of Wollongong to ensure the outcomes will have an application to clinical research and practice and broader service delivery [11]. The protocol is in accord with the Standard Protocol Items Recommendations for Intervention Trials (SPIRIT) guidelines (see Table 1).

**Table 1 Tab1:** SPIRIT table

Domain	Measure	Study period						
		Recruitment	Baseline	Randomisation	Intervention			Follow-up
Week		**0**	**0**	**0**	**4/16**	**16/36**	**4/36**	**52**
**Contacted by**		**CP**	**CP**	**CP**	CP	**CP/RA**	**CP/RA**	**RA**
**Enrolment**								
Eligibility screen		**X**						
Informed consent								
Diagnostic assessment			**X**					
Allocation			**X**					
**Intervention**								
Group skills programme (12 weeks)					Weeks 4–16			
Group skills programme (16 weeks)					Weeks 20–36			
Treatment as usual					Weeks 4–36			
**Assessments**								
Diagnostics	SCID-5-CV		**X**					
	SCID-5-PD		**X**					
Personality traits	PID-5-BF		**X**					**X**
	SA-SAPAS		**X**					**X**
	MSI-BPD			**X**	**X**	**X**		**X**
Executive functioning	BRIEF-A		**X**					**X**
Mental health	K-10		**X**		**X**	**X**		
	MHI-5			**X**	**X**	**X**		**X**
	FFMQ-SF			**X**	**X**	**X**		
	ISAS			**X**	**X**	**X**		
	DERS			**X**	**X**	**X**		
	BDI suicidal ideation item			**X**	**X**	**X**		**X**
	Self-harm (developed items)			**X**	**X**	**X**		**X**
	DEQ-SC6			**X**	**X**	**X**		**X**
	Single item based on the DES			**X**	**X**	**X**		**X**
Quality of life and psychosocial functioning	GAF		**X**					**X**
	SOFAS		**X**					**X**
	HONOS		**X**		**X**	**X**		
	APQ-6		**X**		**X**	**X**		
	WHO-QOL BREF items			**X**	**X**	**X**		**X**
	WHO-DAS items			**X**	**X**	**X**		**X**
	Global Health item			**X**	**X**	**X**		**X**
Relationships and attachment	Support person developed items			**X**	**X**	**X**		**X**
	RQ			**X**	**X**	**X**		**X**
	ORS						**X**	
Therapeutic alliance and engagement	Engagement in treatment (developed items)					**X**		
	Treatment satisfaction (developed items)					**X**		
	Penn Helping Alliance Questionnaire					**X**		
	SRS						**X**	
Biological measures	Saliva samples				**X**	**X**	X	

*Note*: X—administered at time point

*SCID-5-CV* Structured Clinical Interview for DSM-5 Disorders, *SCID-5-PD* Structured Clinical Interview for DSM-5 Disorders for Personality Disorders, *PID-5-BF* Personality inventory for DSM-5 – Brief Form, *SA-SAPAS* Self-Administered Standardised Assessment of Personality – Abbreviated Scale, *MSI-BPD* McLean Screening Instrument for Borderline Personality Disorder, *BRIEF-A* Behaviour Rating Inventory of Executive Function – Adult Version, *K10* Kessler Psychological Distress Scale, *MHI-5* Mental Health Inventory 5, Five Facets of Mindfulness-Short Form, *ISAS*Inventory of Statements about Self-Injury – Section II. Functions, *DERS* Difficulties in Emotion Regulation Scale, *BDI* Beck Depression Inventory, *DEQ-SC6* Depressive Experiences Questionnaire Self-criticism subscale, *GAF* Global Assessment of Functioning Scale, *SOFAS* Social and Occupational Functioning Assessment Scale, *HONOS* Health of the nation outcome scale, *APQ6* Activity and Participation Questionnaire, *WHO-QOL* World Health Organization Quality of Life BREF, *WHO-DAS* World Health Organization Disability Assessment Scale, *RQ* Relationship Questionnaire Clinical Version, *ORS* Outcome Rating Scale, *SRS* Session Rating Scale, *CP* clinical psychologist, *RA* research assistant

### Participants

Participants referred through the central mental health intake line for treatment for emotional dysregulation, self-harm and suicidal ideation and behaviour will be offered a diagnostic assessment including a semi-structured interview (SCID-5-CV and SCID–5-PD) to confirm the diagnosis of borderline personality disorder. This will be conducted by a clinical psychologist or registered psychologist.

Inclusion criterion: Current diagnosis of BPD—DSM V criteria.

All participants will be 18 years or over due to the trial sites being adult mental health services.

Exclusion criteria: Potential participants will be excluded if they meet the following criteria: (1) unlikely to be able to engage with the intervention (e.g. due to geographical constraints, severe substance use or current mental health symptoms which impair their ability to participate in therapy) and (2) assessed to pose a significant risk to the participant (i.e. they require a higher degree of care than can be provided within the trial).

### Sample size and power analysis

A clinically meaningful difference was defined as a reduction of 16% or more in the number of BPD symptoms, according to the MSI-BPD. This estimate is informed by previous studies using this measure, clinical judgement and existing trials examining shortened skills-based interventions for BPD [21, 22]. For this trial, the difference to be detected was calculated using the mean baseline MSI-BPD score (8.16) and standard deviation (2.08) in Miller et al. [22]. The reduction of 16% represents the within-subject mean symptom reduction at the end of the 16-week treatment block, relative to the individual’s baseline. Thus, based on a power of 80%, an alpha level of .05, the total number of participants required in each group is 40. However, accounting for a drop-out rate of 30%, 58 participants will need to be recruited for each group (N = 116).

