## Objectives

The proposed study aims to evaluate the effectiveness of a stepped-care structured psychological intervention for BPD when compared with treatment as usual. Specifically, the research seeks to answer: Is a stepped approach effective in treating BPD? This will be answered through the following questions.
(i)Is there a difference in outcomes for clients receiving group intervention or treatment as usual?

Hypothesis 1. Patients in the group treatment will demonstrate an equivalent reduction in BPD symptoms to participants in the treatment as usual (TAU) condition.
(ii)Do changes in symptoms and functioning during treatment persist following treatment?

Hypothesis 2. Participants in the group treatment will report an equivalent reduction in BPD symptom severity to participants in the TAU condition following treatment.
(iii)What implications does a stepped-care approach have for health services (including economic, treatment focus)?

Hypothesis 3. Participants in the group treatment will experience an equivalent reduction in length of admission and acute care following treatment compared to participants in the TAU condition.

This study is being conducted within two community mental health services which positions it as a pragmatic trial designed to provide valuable information regarding the real-world effectiveness of stepped-care treatment for BPD compared to existing care (treatment as usual).

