### Trial status

The trial is registered with the Australian New Zealand Clinical Trials Registry - ACTRN12618000477224. It was first registered prospectively on 3/04/2018 and updated on 11/03/2020. TRGS protocol version 1, date of protocol: 17/08/2017. Data recruitment commenced on 5/10/2018. To date, 125 participants have been recruited to the study. It is anticipated that recruitment will be completed by October 2020.

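### The 80% power rests on a 16% reduction defined as a within-subject change, while the primary test compares change between arms, so that power is not established for the primary test

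*Protocol article*

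**What the plan says.** Under Sample size and power analysis, the protocol article sets the target as follows: "A clinically meaningful difference was defined as a reduction of 16% or more in the number of BPD symptoms", measured on the MSI-BPD. The difference is computed from a baseline mean of 8.16 and SD of 2.08 taken from an earlier study. The article then says what the 16% is: "The reduction of 16% represents the within-subject mean symptom reduction at the end of the 16-week treatment block", measured against each patient's own baseline. The next sentence draws the sample size from it: "based on a power of 80%, an alpha level of .05, the total number of participants required in each group is 40". With 30% dropout this becomes 58 per group, 116 in total.

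Under Primary analyses, effectiveness is judged by the group × time interaction in a linear mixed model. The change from baseline to the end of the 16-week block is of primary interest.

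Two other places bear on what TAU patients are expected to do. Study design describes TAU as a tailored set of active services, including case management, rehabilitation and referral to psychologists or psychiatrists with experience of BPD. Under Objectives, Hypothesis 1 predicts an equivalent symptom reduction in the two arms. Hypothesis 2 says the same of the period after treatment: "Participants in the group treatment will report an equivalent reduction in BPD symptom severity to participants in the TAU condition following treatment".

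**The concern.** A within-subject reduction describes how far one arm moves from its own baseline. The interaction tests how much further one arm moves than the other. The two are equal only when the comparator does not move. The sample size paragraph defines the first quantity, and the analysis tests the second. No TAU change is stated that would link them.

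The SD has a similar gap. The value 2.08 is the spread of scores at baseline. The spread of change scores depends on the correlation between baseline and the end of the block, which is not given.

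What is at stake is how a non-significant interaction is read. The hypotheses predict equivalent reductions, so a null result could easily be presented as the finding of a trial with 80% power. On the article's own definition of the effect, the power could be well below that.

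**Working it through.** **Inputs from the document.** Relative reduction 16%, baseline mean 8.16, SD 2.08, alpha .05, power 80%, dropout 30% (Sample size and power analysis); 1:1 allocation (Participant randomisation). Sidedness is not stated; two-sided reproduces the figure.

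**Reproducing the plan's figure.**
- Difference: 0.16 × 8.16 = 1.306 points. Standardised: 1.306 / 2.08 = 0.628.
- Two independent arms, normal approximation: n = 2 × [(1.960 + 0.842) × 2.08 / 1.306]² = 39.8, so 40 per arm. The t-test version gives 40.8.
- Dropout: 40 / 0.70 = 57.1, so 58 per arm.

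The stated 40 and 58 are therefore matched with 1.31 points as the between-arm gap.

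**What this implies.** If the group arm falls by 16% and the between-arm gap is also 16% of baseline, the TAU fall is 16% − 16% = 0. With equal SDs at both times, SD of change = 2.08 × √(2(1 − r)), where r is the baseline to end-of-block correlation. This equals 2.08 only at r = 0.5.

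**Power over the unstated TAU change.** Assumptions: group arm falls 16%, SD 2.08, 40 completers per arm, two-sided t-test. Gap = (0.16 − TAU fall) × 8.16.

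| Assumed TAU fall | Gap (points) | d | Power |
|---|---|---|---|
| 0% | 1.306 | 0.628 | 79% |
| 2% | 1.142 | 0.549 | 68% |
| 4% | 0.979 | 0.471 | 55% |
| 8% | 0.653 | 0.314 | 28% |
| 12% | 0.326 | 0.157 | 11% |

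**Power over the unstated correlation.** Assumptions: no TAU change, gap 1.306, change-score t-test, 40 per arm.

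| Assumed r | SD of change | Power |
|---|---|---|
| 0.3 | 2.46 | 65% |
| 0.5 | 2.08 | 79% |
| 0.7 | 1.61 | 95% |

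**Both together.** At r = 0.7, change-score power stays at about 80% with a TAU fall of 3.5% (gap 0.125 × 8.16 = 1.02; 1.02 / 1.61 = 0.63). At a TAU fall of 8% and r = 0.7 it is 43%, or 49% with baseline adjustment (ANCOVA).

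**Effect of the count to date.** Trial status reports that "125 participants have been recruited to the study", with recruitment still open. If 125 were final, 125 × 0.70 / 2 is about 44 per arm. At SD 2.08, power would then be 83%, 72%, 59%, 31% and 11% for the five TAU falls in the first table.

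**The case against.** The strongest defence is that the paragraph also speaks of a clinically meaningful difference and of a difference to be detected. Those words fit a between-arm target. On that reading the gap is 1.31 points by definition, the power does not depend on what TAU does, and the fault is one badly worded sentence. This stands as a possible intention, and the fix allows for it. It does not rescue the text, because the sentence that leads directly to the 40 defines the reduction as within-subject.

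A reader might infer that 80% power holds only if TAU patients do not improve at all. The document does not support so strong a claim. Zero TAU change is not sufficient, since at r = 0.3 power is 65% even then. It is not necessary either, since at r = 0.7 about 80% is kept with a 3.5% TAU fall. The target is also worded as 16% or more, so a larger fall in the group arm could leave a 16% gap over an improving TAU arm, although no larger figure is given.

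A reader might also infer that the arithmetic proves how the 40 was obtained. It does not. A paired calculation by normal approximation at r = 0, with SD of change 2.08 × √2, also gives 39.8. That route would fit the interaction test no better, but the two-sample origin remains an inference from a match.

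The conflict between equivalence hypotheses and a superiority design is a separate inconsistency. It is used here only to show that no TAU change is not what the protocol expects. That power equals alpha when the arms fall equally is true of any superiority test and adds nothing.

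Finally, this is not a detail left to an analysis plan. The article states the calculation in full and defines its effect in a way that does not match its test.

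**Conclusion.** The point holds: as written, the 80% power is not established for the primary test. The arithmetic is correct, but the quantity entered is not the one tested. With a 16% fall in the group arm, the quoted power requires a TAU change of about zero together with an SD of change of about 2.08, or some other combination of TAU change and correlation that the document does not give.

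Over the assumed ranges, power at 40 per arm runs from 79% down to 11% as the TAU fall goes from 0% to 12% at SD 2.08. It runs from 65% to 95% as the correlation goes from 0.3 to 0.7 with no TAU change. These are ranges, not estimates. They do not show that the trial is underpowered or that it needs more patients. They show that the stated figure cannot be relied on when a null interaction is interpreted.

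**What to change.** Rewrite the sample size paragraph in one of two ways, not a mixture.

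(a) If the 16% is the expected within-arm change, keep that definition. State the assumed TAU change and the assumed baseline to end-of-block correlation. Replace the 80% with the resulting power for the group × time interaction, in a short table over both assumptions, at the planned 40 completers per arm and at the final number recruited. The 125 under Trial status is an interim count and should not be used as the final one.

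(b) If a between-arm target was intended, delete the within-subject sentence. State that the trial has about 80% power only for a fall 1.31 points greater than under TAU (an excess of 16% of baseline), at a stated correlation. Say that smaller advantages over active TAU are not powered. A table over TAU change does not belong here, because the gap is then fixed by definition.

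In either case, do not describe a non-significant interaction as the result of a trial with 80% power for a 16% within-subject reduction.

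The cost is one paragraph, with no extra patients and no change to the analysis. The downside is that the stated power becomes less favourable under (a) or narrower in scope under (b).

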### Participant randomisation

Following diagnostic assessment, participants will be randomly allocated to one of the treatment arms using a computerised randomisation programme, QMinim. QMinim uses a minimization method to generate an imbalance score for each participant based on prognostic factors. Allocation is then made to ensure minimum imbalance between the groups. Randomness is incorporated into the generated algorithm to maintain blindness [28]. Blocking is used to ensure equal numbers within each condition. Participants will be allocated to each treatment arm on a 1:1 ratio. Minimization prognostic factors are age, gender, GAF score severity, self-harm ideation and suicide attempts to control for these variables and allow for balanced groups. Treatment allocation will be concealed from the researchers administering assessments to prospective participants to ensure bias cannot be introduced into the allocation process.

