#### Primary analyses

The effect of treatment on primary outcomes will be evaluated using a linear mixed models approach, to account for the repeated measured structure of the data (SPSS-25). The data will be analysed as an intention-to-treat with time as a repeated measure. Recommended as the gold standard for study designs of this nature, this design (i) allows for the assessment of individual trends over time, with sensitivity to detect change; (ii) takes into account the longitudinal nature, utilising all data available; and (iii) controls for any pre-intervention differences [9, 27]. A linear mixed models analysis will be performed for each primary outcome variable symptom reduction (total number of BPD symptoms measured by the MSI-BPD) and service utilisation (inpatient hospital admissions and emergency department presentations). Change over time on these variables will be modelled as a within-subject effect of time, and the effectiveness of the intervention conditions will be determined by significant two-way group × time interaction. Although the change between baseline and end of the 16-week treatment block is of primary interest, three time points will be included to also examine the change during treatment and whether any changes are maintained following treatment. Within- and between-group effect sizes will be calculated, compared and interpreted according to the Cohen [5] recommendations.

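### Allocation is minimised on five prognostic factors that the described primary model does not name; where they predict change in MSI-BPD, the unadjusted group × time test is conservative and loses power

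*Protocol article*

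**What the plan says.** Under Participant randomisation, the article uses a computerised minimisation programme: "Minimization prognostic factors are age, gender, GAF score severity, self-harm ideation and suicide attempts to control for these variables and allow for balanced groups". The allocation is not fully deterministic: "Randomness is incorporated into the generated algorithm to maintain blindness". The target is equal arms: "Participants will be allocated to each treatment arm on a 1:1 ratio". The same section also says that blocking is used to keep the numbers per condition equal. Site is not among the minimisation factors, although Study setting says: "Approximately 80% of participants will be recruited at trial site 1 with the remaining 20% recruited at trial site 2".

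Under Primary analyses, "The data will be analysed as an intention-to-treat with time as a repeated measure". Change over time is a within-subject effect, and "the effectiveness of the intervention conditions will be determined by significant two-way group × time interaction". The article says that this design "controls for any pre-intervention differences". No covariate is named there, and none is ruled out.

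**The concern.** The five factors were chosen because they are thought to be prognostic, and the allocation is built to balance them. Balance reduces the true sampling variance of the treatment contrast. An analysis without the factors does not see this reduction: it leaves their variance in the residual and computes a standard error as if allocation had been simple. The nominal 5% test then rejects less often than 5% under the null, and the precision that the design bought is not collected.

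The statement that the model deals with differences before the intervention does not fill the gap. Comparing change from baseline handles the outcome's own starting level and any factor effect that is constant over time. It does not remove variance due to factors that predict how much a patient changes. At stake are calibration and efficiency of the main comparison, on variables already collected before allocation.

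**Working it through.** **Inputs.** From Sample size and power analysis: baseline mean MSI-BPD 8.16, SD 2.08, reduction 16%, power 80%, alpha 0.05, dropout 30%. From Participant randomisation: five factors, 1:1 ratio, a random element of unstated strength. Assumed, because the documents give no figure: R², the share of variance in change explained by the five factors, from 0 to 0.30. As in the plan, 2.08 serves as the SD of the quantity compared.

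**The plan's own figure.** Difference = 0.16 × 8.16 = 1.3056; standardised, 1.3056 / 2.08 = 0.628. Two-sided n per group = 2 × (1.960 + 0.842)² / 0.628² = 39.8, so 40. With dropout, 40 / 0.70 = 57.1, so 58. Both stated figures reproduce.

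**Near-perfect balance, 40 per group.** The expected z is 0.628 / √(2/40) = 2.807. If the factors explain R² and are balanced, the true standard error is √(1 − R²) times the one that the unadjusted model reports. So:

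- true size, unadjusted = 2 × [1 − Φ(1.96 / √(1 − R²))]
- power, unadjusted = Φ((2.807 − 1.96) / √(1 − R²))
- power, adjusted = Φ(2.807 / √(1 − R²) − 1.96)

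| R² of change | True size, unadjusted | Power, unadjusted | Power, adjusted |
|---|---|---|---|
| 0 | 5.0% | 80.2% | 80.2% |
| 0.05 | 4.4% | 80.8% | 82.1% |
| 0.10 | 3.9% | 81.4% | 84.1% |
| 0.20 | 2.8% | 82.8% | 88.1% |
| 0.30 | 1.9% | 84.4% | 91.9% |

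Worked line, R² = 0.20: √0.80 = 0.894; 1.96 / 0.894 = 2.191, size 2.8%; 0.847 / 0.894 = 0.947, power 82.8%; 2.807 / 0.894 − 1.96 = 1.179, power 88.1%.

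**Imperfect balance.** A simulation minimised 116 patients on five binary factors with an assumed 0.8 probability of the favoured arm, kept a random 80 for analysis, and compared arms on one continuous outcome (3,000 runs per cell; Monte Carlo error about 0.4 points on size).

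| R² | Size, unadjusted | Size, adjusted | Power, unadjusted | Power, adjusted |
|---|---|---|---|---|
| 0 | 5.8% | 5.5% | 79.1% | 78.0% |
| 0.10 | 4.0% | 4.4% | 80.2% | 82.1% |
| 0.20 | 3.4% | 4.8% | 79.9% | 85.8% |
| 0.30 | 2.1% | 4.7% | 81.0% | 89.8% |

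The direction is the same and the gains are somewhat smaller. At R² = 0 adjustment gains nothing and may cost about a point of power.

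**Site.** In the same simulation, with site explaining 5% and the factors nothing, size was 4.1% unadjusted and 4.9% with factors and site, and power was 80.0% and 80.3%. Omitting site did not inflate the error rate. For chance imbalance: 20% of 116 is about 23 patients at site 2. With arms fixed at 58:58, the hypergeometric probability of a 15:8 split or worse, in either direction, is about 16%.

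**The case against.** The strongest reply is that this argues from silence. The article does not list all fixed effects, it excludes no covariate, and a covariate list is commonly left to an analysis plan that is not shown. That stands in part: one can say only that the model as described does not name the factors, not that the trial will omit them. But the section is not merely silent. It fixes the deciding test and says how earlier differences are controlled, and that mechanism does not do the work for factors that predict change.

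The second reply is that the size is unknown. This stands in full. R² is assumed, it must refer to change and not to the outcome level, and it could be near zero. The gain must also be counted against unadjusted power under the same balance, not against the planned 80%.

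Two stronger readings are tempting, and the documents support neither. A reader might infer that the primary test is invalid or produces too many false positives; the error runs the other way. A reader might also infer that leaving out an unequally recruiting site makes the standard errors wrong. That argument needs balance forced by the allocation, and site was not minimised. Chance imbalance by site does not bias a randomised comparison. The 16% above describes only how often the split would be uneven; independent coin tosses would give 21%, but they ignore the equal arm sizes that the article promises.

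**Conclusion.** The point holds as one of efficiency and calibration. Followed as described, the group × time test is conservative wherever the five factors predict change in MSI-BPD. With R² of change between 0.10 and 0.30 and near-perfect balance, size falls to between 3.9% and 1.9%, and adjustment adds about 3 to 7 points of power (81.4% to 84.1% at the low end, 84.4% to 91.9% at the high end). In the simulation with a random element the gain was about 2 to 9 points, because unadjusted power stayed near 80%; adjusted power was lower than in the ideal case. With R² near zero there is nothing to gain.

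These figures rest on the assumed R², the plan's SD and effect, 80 evaluable patients and, for the simulation, the assumed strength of the random element. The sample size is unaffected. The change is worth making, but results without it would not be invalid.

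**What to change.** Prespecify age, gender, GAF severity, self-harm ideation and suicide attempts as fixed effects in the primary mixed model, in one of two forms:

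- If baseline MSI-BPD stays in the outcome vector, enter each factor with its interaction with time. With complete data, main effects alone leave the group × time estimate unchanged.
- If baseline MSI-BPD is moved to a covariate, main effects of the five factors are enough.

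Use the same covariates in the service-use analyses. Site may be added for precision, but the validity of the standard errors does not require it.

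The cost is one sentence in the plan and some degrees of freedom. With three time points and each factor entered as a single term, the first form uses 5 main effects and 5 × 2 = 10 interactions, 15 in all (18 with site: 6 + 12). The second uses 5, plus baseline. With about 80 evaluable patients the second is the more economical. Trial status reports 125 participants already recruited, so the allocation scheme can no longer be changed for most of the trial, and the analysis is where this can be put right. As the trial is not blinded, the covariates should be fixed before outcomes are analysed.
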